#### 2.2.6 Carer and patient recruitment.

Local cardiology teams will identify and approach potential participants during routine, in and out-patient HF appointments. Eligible patients will receive information packs for both them and their carer. Those interested in participation will provide permission to be contacted by the research team for recruitment. During this contact, patients will also signpost the research team to their interested carers. Subsequently, these carers will be contacted by the research team for eligibility screening and recruitment. The collaborating hospital sites cover regions with a range of socio-demographic characteristics (*i.e.,* education level, socio-economic status, and ethnicity), which will maximise the diversity of the recruited sample.

#### 2.2.7 Healthcare professionals.

Healthcare professionals (*i.e.,* HELP delivery staff, cardiologists, and HF nurses) across the collaborating sites will be invited to provide process evaluation data. These individuals will be supplied with information sheets and will be asked to contact the research team if interested in participation. Healthcare professionals will be eligible if they are 1) Members of the cardiology team, 2) Aged 18 years or older, and 3) Willing to provide informed consent.

#### 2.2.8 Intervention design.

HELP design was based on prior literature and comprehensive input from carers of patients with HF and healthcare professionals, with the co-development and feasibility testing of this intervention previously reported in detail [10]. HELP constitutes a six-week, nurse-led, psychoeducational programme comprising two components:

1)
*Online support group sessions*

Nurse-led, weekly online support group sessions are delivered to groups of approximately twelve carers over a six-week period. Each session lasts sixty minutes and is underpinned by a standardised, educational presentation covering the topics displayed in Table 1. Following each educational presentation, the HF nurse facilitates a group discussion to issue tailored advice, guidance, and signposting, along with providing a platform for carers to engage in peer support.

**Table 1 pone.0347037.t001:** Support Group Schedule.

Session Number	Topic	Content
1	Introduction	Group introductions Summary of HELP content Guidance on access and usage of self-directed educational resources (booklet and website)
2	Understanding HF	Overview of HF Symptoms Prognosis Palliative care
3	Personal Wellbeing	Looking after physical and emotional wellbeing Management strategies for complex emotions
4	Communication and Support	Communicating with loved ones and healthcare professionals
5	Practical Skills for Supporting Self-Management	Controlling diet and salt intake Management of fluid and medication Exercise Monitoring symptoms at home
6	Feedback	Discussion of experience and final comments/ questions Feedback on HELP and areas of improvement

**Legend** HELP = HEart faiLure carer support Programme and HF = heart failure.

2)
*Self-directed, educational resources (booklet and website)*

Upon HELP enrolment, carers will receive an educational booklet (S3 Text) and access to a supplementary website. Both resources were co-designed and professionally produced. The educational booklet complements the online support group sessions by facilitating self-directed learning across the following five chapters:

Chapter 1: What is HF?Chapter 2: Planning for the futureChapter 3: Looking after yourselfChapter 4: CommunicationChapter 5: Your role as a carer

Each chapter is completed over the week leading to the corresponding online support group session. The self-directed website supplements the booklet by presenting the same educational information in a potentially more engaging format (*i.e.,* animations, interactive content, and topic summaries). Additionally, the website provides access to the standardised educational presentations for the online support group sessions, along with facilitating the submission of non-urgent questions for the HF nurse to answer at the subsequent online support group session.

HELP is underpinned by the Transactional Theory of Stress and Coping [18], which postulates that adaptive coping strategies can moderate the relationship between the perception of potentially stressful experiences and negative outcomes (*i.e.,* burnout and distress). By facilitating improved access to information and support from peers and healthcare professionals, the intervention will deliver key practical and emotional coping resources to alleviate stress, burden, and improve carer wellbeing, ultimately empowering carers in their caregiving role. The intervention components are mapped to the Theoretical Domains Framework, which facilitates further theoretical grounding of the mechanisms of impact for behavior change [19]. Consistent with MRC guidance for complex interventions [20], Fig 2 presents a preliminary logic model illustrating the key aspects of HELP, which will evolve according to the results of this study.

**Fig 2 pone.0347037.g002:**
[figure not shown]
HELP Logic Model. **Legend** HF = Heart Failure; QoL = Quality of Life; UK = United Kingdom; HELP = HEart faiLure carer support Programme; HSC = Health and Social Care; NHS = National Health Service; and in parentheses () and italics = mapping to Theoretical Domains Framework.

#### 2.2.9 Intervention delivery.

HELP will be delivered by local specialist HF nurses across the collaborating sites. Following recruitment, carers will be assigned a start date for HELP. One week prior to the first online support group session, carers will receive the educational booklet and access to the supplementary website, along with supporting programme materials (*i.e.,* online support group schedule and guidance on joining online sessions). Carers will be advised to read each chapter of the educational booklet and supplementary website before the corresponding online support group session. The online support group sessions will run on ‘Zoom’, with a link and password to each session issued to carers before commencement. Carers will receive a reminder email two days before each online support group session. The research team will remain in contact with all participants to provide ongoing support with accessing the online support group sessions and supplementary website.

The nurse-led, online support group sessions will be delivered using an informal approach to facilitate a comfortable environment for the carers. Each session will consist of twelve carers and last approximately sixty minutes. The sessions will initiate with a standardised, educational presentation (approximately 20 minutes) on the allocated topic, with the remainder of the session (approximately 40 minutes) dedicated to questions raised during the session or submitted via the website; group discussion; tailored advice and signposting; and peer support. Carers will receive the option of having their cameras switched on or off during the sessions and will be encouraged to use the chat function to ask questions if unwilling to speak in front of the group.

Five programme rollouts of HELP (six weeks each) will be delivered across each of the three collaborating nations over a year period, with twelve carers per rollout (60 carers per nation; 180 carers in total). Rollouts will be separated by four-week windows, which will account for staff holidays and provide recruitment intervals for the subsequent rollout.

#### 2.2.10 Implementation strategy.

The development of implementation strategies is an evidence-based method of promoting uptake of a novel intervention by healthcare professionals [21]. Accordingly, guided by the NPT framework [14], we engaged with healthcare professionals (approximately forty HF nurses and cardiologists) across our five collaborating sites in the UK to co-develop a multi-faceted implementation strategy for HELP, which is theoretically grounded across: 1) Coherence (*i.e.,* does the intervention make sense?), 2) Cognitive participation (how do people engage?), 3) Collective action (how do people work with the intervention?), and 4) Reflexive monitoring (how do people appraise the intervention?). This iterative, developmental process spanned three, one-hour stakeholder meetings, resulting in the identification of four principal implementation agents (1. HELP Delivery Staff, 2. Referral staff, 3. Clinical Leadership, and 4. Carers). A multi-faceted implementation strategy was developed based on clinical and academic input, which employs tailored methods of supporting HELP implementation for each of the implementation agents (S4 Table).

Depending on preference, intervention delivery staff will receive online or in-person training from the project team, which will employ an interactive approach including content talks, case scenario discussions, and role plays. This training programme will familiarise delivery staff with intervention design and cover essential skills for implementation (*i.e.,* effective communication, building trusting relationships, managing conflict, and delivering behaviour change techniques). These staff will also receive access to standardised intervention materials and support documents (*i.e.,* intervention protocol and fidelity checklist), with regular support and monitoring by the project team at and between Steering Group meetings. As detailed in S4 Table, the other key implementation agents (*i.e.,* HELP referral staff, clinical leadership, and carers) will be supported via communication with the research team, information from project documents (*i.e.,* screening log and information sheets), and monitoring at Steering Group meetings.

### 2.3 Outcomes

An overview of the study flow and data collection process is presented in Fig 3. Guided by CFIR and NPT integration [13,14], quantitative (*i.e.,* questionnaires, logs, and checklists) and qualitative (*i.e.,* interviews) data will be collected across the participants at five time points: 1. Baseline, 2. Intra-intervention, 3. Post-intervention (six weeks), 4. Six months post-intervention, and 5. Study end (eighteen months). For questionnaire data, participants will have the option of completion via Microsoft Forms or telephone calls, depending on preference.

**Fig 3 pone.0347037.g003:**
[figure not shown]
Study Flow and Data Collection Process. **Legend** UK = United Kingdom; HELP = HEart faiLure carer support Programme; GP = General Practitioner; HF = heart failure, and LVEF = left ventricular ejection fraction.

#### 2.3.1. Demographic characteristics.

Participants will be asked to complete a demographic questionnaire at baseline (*i.e.,* age, gender, ethnicity, education level, employment status, and duration of care provision). These data will be used to contextualise the samples and findings.

#### 2.3.2 Process evaluation.

The multi-faceted implementation strategy will be assessed via a process evaluation of acceptability, fidelity, and context of HELP delivery across the collaborating clinical sites. Consistent with the framework published by the National Institutes of Health Behaviour Change Consortium [22], the fidelity examination will include the following:

Study design: Protocol and intervention deviations will be documented and reported in implementation and HELP delivery staff logs.Provider training: Following training, intervention competency of HELP delivery staff will be assessed during a ‘role play’ session with a fidelity checklist.Intervention delivery: Online support group session recordings will be evaluated using an intervention fidelity checklist spanning: 1) Interactional style (*i.e.,* carer-centred approach); 2) Intervention components covered and those omitted; 3) Components added; 4) Dosage (*i.e.,* session duration and attendance); and 5) Competency (*i.e.,* maintenance of skill set).Treatment receipt and enactment: Carers’ understanding of the information provided and ability to implement the skills and recommendations delivered by HELP will be investigated via bespoke, weekly HELP impact (completed intra-intervention) and long-term adherence questionnaires (completed six months post-intervention), along with deeper exploration via interviews (discussed below).

Contextual factors will be assessed via data (*i.e.,* ‘background noise’ and protocol deviations) recorded in the implementation and HELP delivery staff logs, along with an evaluation of bespoke, intervention acceptability questionnaires completed by carers and HELP delivery staff. Individual, semi-structured interviews (approximately 60 minutes in duration) will also be conducted via telephone calls with participants at 6 months or study end (eighteen months), which will add rich, qualitative data to the assessment of acceptability, fidelity, and context. A “laddered-style approach” will be implemented in the interviews to explore emerging ideas [23], with the topic guides (S5 Text) based on the domains of CFIR and NPT [13,14]. Approximately thirty-three interviews will be conducted with carers (number (*n*) = 10), patients (*n* = 10), HELP delivery staff (*n* = 3), and healthcare professionals (*n* = 10 in total, *i.e., n* = 5 HF nurses and *n* = 5 cardiologists). This sample size is based on recommendations for a study of this scope [24]. A purposive sampling strategy [25] will maximise representation and diversity across the samples (*i.e.,* age, gender, ethnicity, education, and socio-economic status), with equal numbers of cases recruited across the collaborating sites. All interviews will be audio-recorded before verbatim transcription.

#### 2.3.3 Economic evaluation.

The economic cost of intervention implementation in the UK will be estimated via the collection of the following data from implementation and HELP delivery staff logs:

1)Training costs and time input for supervision of HELP delivery staff.2)The time, expenditure, resources required, and adaptations made for HELP implementation by delivery staff.

#### 2.3.4 Participant outcomes.

The short and long-term impact of HELP on outcomes for carers and patients will be assessed across data from validated questionnaires, patient diaries, and medical records (see Table 2). Participant outcome data will be collected at three time points: 1. Baseline, 2. Post-intervention (week six), and 3. Six months post-intervention.

**Table 2 pone.0347037.t002:** Participant Outcomes and Measurement Instruments.

Sample	Outcome	Measurement Instrument	Time Point		
			Baseline	Post-Intervention (Week 6)	6 Months Post-Intervention
**Carers**	Carer Burden	Zarit Burden Interview, Short Form [26]	X	X	X
	Carer Preparedness	Preparedness for Caregiving Scale [27]	X	X	X
	QoL	12-Item Short Form Survey [28]	X	X	X
	Anxiety and Depression	Hospital Anxiety and Depression Scale [29]	X	X	X
	Stress	Perceived Stress Scale [30]	X	X	X
	Social Support	Multidimensional Scale of Perceived Social Support [31]	X	X	X
**Patients with HF**	Disease-specific, QoL	Minnesota Living with HF Questionnaire [32]	X	X	X
	Generic, QoL	EuroQoL Five Dimension Questionnaire [33]	X	X	X
	GP Visits with Reasons over Previous 6 Months	Bespoke, Recall Questionnaire at Baseline and Patient Diary Self-Completed from Baseline to 6 Months	X		X
	Most Recent LVEF Measurement	Medical Record	X		X
	Hospital Admissions with Reasons over Previous 6 Months	Medical Record	X		X

**Legend** QoL = Quality of Life; HF = Heart Failure; GP = General Practitioner; and LVEF = Left Ventricular Ejection Fraction.

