### 2.5 Data analysis

#### 2.5.1 Quantitative data.

Quantitative data analysis will be managed on Statistical Package for the Social Sciences (IBM SPSS Statistics, Version 31). Continuous data will be presented as mean ± standard deviation, with discrete data reported as absolute numbers and percentages. Categorical data will be displayed as frequency/ percentages. For participant outcomes, repeated measures analysis of variance will be used to investigate the effect of time point on outcome scores. Due to the absence of statistical power, the results will be used to identify preliminary evidence of promise for the intervention across different participant outcomes, with potential effect sizes generated to inform the required sample size for a future definitive evaluation.

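### GP visits are recalled at baseline but kept by diary at follow-up, so the before-after change cannot be separated from the change of instrument, and the follow-up window is labelled inconsistently

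*Protocol article*

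**What the plan says.** Section 2.3.4 of the protocol article sets the schedule for outcomes: "Participant outcome data will be collected at three time points: 1. Baseline, 2. Post-intervention (week six), and 3. Six months post-intervention". In Table 2 the row "GP Visits with Reasons over Previous 6 Months" is marked at the first and third of these only. Its instrument cell reads "Bespoke, Recall Questionnaire at Baseline and Patient Diary Self-Completed from Baseline to 6 Months".

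The other healthcare-use row, "Hospital Admissions with Reasons over Previous 6 Months", carries the same window label and the same two marks, but draws on the medical record both times.

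Section 2.3 counts follow-up from the end of the programme: "3. Post-intervention (six weeks), 4. Six months post-intervention, and 5. Study end (eighteen months". Section 2.3.2 uses six months without that qualifier when it places the interviews "with participants at 6 months or study end (eighteen months".

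For the analysis, section 2.5.1 says that "repeated measures analysis of variance will be used to investigate the effect of time point on outcome scores". The same section intends the results to show early promise and to supply effect sizes for the sample size of a later definitive study. Section 3.1 names the non-randomised design and the lack of power as limitations. It does not mention the change of instrument.

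**The concern.** Every patient moves from recall to diary between the two measurements, and there is no comparison group that makes the same move. Time point and instrument are therefore the same variable in the data, and no analysis of these two measurements alone can tell them apart. A larger sample would not help, because this is bias and not imprecision.

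The observation period adds a second uncertainty. The row label gives a look-back of six months, the instrument cell gives a diary that starts at baseline, and the column heading places follow-up six months after a programme that itself lasts six weeks. These three do not fix one window.

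At stake is one of the two healthcare-use outcomes under the third objective (section 1.2). An apparent fall or rise in GP visits could be taken as a signal, and its size carried into the planning of the next study, when part or all of it comes from how the visits were counted.

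**Working it through.** The article states no GP-visit rate, no expected change and no capture rate for either instrument, so there is no figure of its own to reproduce here. The check asks what follow-up to baseline ratio would appear if the true visit rate did not change.

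**Inputs**
- Programme length: 6 weeks (section 2.2.8: "Nurse-led, weekly online support group sessions are delivered to groups of approximately twelve carers over a six-week period").
- Baseline window: six months (Table 2), which is 6 × 365.25 / 12 / 7 = 26.1 weeks.
- Follow-up contact: six months after the end of the programme (sections 2.3 and 2.3.4).
- Gap from baseline assessment to first session: not given in the text. Section 2.2.9 says only that materials go out one week before the first session. Assumed 0 to 4 weeks.
- Share of true visits captured by each instrument: not given. Assumed 80 to 100% for recall and for diary alike.

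**Formula**

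Apparent ratio = (follow-up weeks / baseline weeks) × (diary capture / recall capture).

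**Step 1: instrument alone, equal windows**
- Full recall, diary at 80%: 0.80 / 1.00 = 0.80.
- Recall at 80%, full diary: 1.00 / 0.80 = 1.25.
- Equal capture by both: 1.00.

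The artefact can therefore go either way.

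**Step 2: window alone, under the three readings of the row**

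| Reading of the diary period | Follow-up weeks | Ratio to 26.1 |
|---|---|---|
| Baseline to six months post-intervention, all entries counted, no gap | 6 + 26.1 = 32.1 | 1.23 |
| Same, 1-week gap | 33.1 | 1.27 |
| Same, 4-week gap | 36.1 | 1.38 |
| Stops six months after baseline | 26.1 | 1.00 |
| Runs to six months post-intervention, last six months counted | 26.1 | 1.00 |

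Under the reading that stops six months after baseline, the lengths match. With no gap, however, only 26.1 − 6 = 20.1 weeks follow the programme, so the diary ends before the contact named in the column heading. The last reading agrees with both the row label and the column heading, but the article does not state it.

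**Step 3: both together, on the longest reading with no gap**
- Lowest: 1.23 × 0.80 = 0.98.
- Highest: 1.23 × 1.25 = 1.54.

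**Step 4: what removes each part**

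One fixed six-month window brings the window ratio to 1.00 but leaves the 0.80 to 1.25 from Step 1. Only the same instrument at both time points addresses that.

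**The case against.** The strongest reply is that the row label governs both marked time points. Section 2.3.2 appears to use a bare six months as shorthand for the post-intervention contact, so the diary would run to that contact and the last six months would be counted. The windows are then equal. This is a fair reading. A reader might infer from the instrument cell that follow-up is definitely longer than baseline, but the documents do not establish that. They show inconsistent labels, not a longer period.

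For the same reason the article does not support saying that admissions use another window: both rows carry the same label.

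A reader might also derive a large spurious rise. With recall at 70 to 90%, a complete diary and a gap of 0 to 4 weeks, the arithmetic gives 1.23 / 0.90 = 1.37 up to 1.38 / 0.70 = 1.98. That holds only on the longest reading and treats a self-completed diary kept for more than seven months as perfect. Missed entries push the other way, and recall can also over-count.

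It may be said that repeated measures analysis of variance suits counts poorly. Section 2.5.1 speaks of scores, so its application to counts is unclear, and count models and exposure terms commonly belong in an analysis plan that is not shown. That is not part of this point.

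Two further arguments have weight. No prospective diary can exist before enrolment, so a patient-reported baseline has to be recalled. And GP visits are one of eleven exploratory rows in Table 2, in results the article itself calls preliminary. They do not enter the economic analysis, which costs delivery only (sections 2.3.3 and 2.5.4).

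None of this touches the change of instrument, which the table states explicitly and the limitations omit.

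**Conclusion.** The point stands on the instrument. As Table 2 is written, the before-after change in GP visits cannot be interpreted as a change in visits, whichever window is meant. With no true change the apparent ratio could lie between 0.80 and 1.25, on the assumption that each instrument captures 80 to 100% of visits. The sign of the bias is unknown.

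On the window, the finding is narrower: three labels in one row are not reconciled. The ratio from window length is 1.00 if six months of diary are counted, and 1.23 or more if the whole diary to the post-intervention contact is counted. The text does not say which. Figs 1 and 3, which show the schedule and data flow, were not available for this check and should be consulted.

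Severity is modest. The outcome is exploratory, and an uncontrolled change would not isolate the programme's effect even with one instrument. It is still worth correcting because effect sizes from this study are meant to inform the next one, and because a matching recall measure cannot be properly recovered once the six-month contacts have passed.

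**What to change.** 1. Give patients the same bespoke recall questionnaire again at the existing six-month post-intervention contact, and use it for the before-after comparison. Keep the diary as supplementary prospective data.
2. State in Table 2 that the follow-up window for both GP visits and admissions is the six months before that contact. Count only diary entries inside it, or report visits per month of observed time.
3. List the instrument change as a limitation wherever a diary-based change is reported, and when any GP-visit effect size is carried into the future study's sample size.

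The cost is a few minutes of patient time, a change to the Table 2 wording, and an amendment with the approvals described in section 2.6. The second recall may be aided by months of diary-keeping, so the match with baseline will be imperfect, though closer than recall against diary. The change should be in place before the first six-month contacts.

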#### 2.2.4 Carers.

The target population of HELP is informal carers of patients with symptomatic HF. These individuals will be eligible to participate if they are: 1) Aged 18 years or older; 2) Physically and mentally capable of operating a digital device; 3) Able to engage comfortably in conversation with peers and capable of reading written materials; 4) Caring (regular, unpaid care) for a person with a clinical diagnosis of HF who is receiving standard evidence-based HF therapies and has either HF symptoms or one episode of decompensation (symptoms requiring medical attention) in previous six months; and 5) Capable of speaking and understanding English.

There will be five programme rollouts of HELP (six weeks each) across each of the three collaborating nations over a one-year period, with twelve carers per rollout (60 carers per nation; 180 carers in total). This sample size was pragmatically determined by the maximum study duration within the funding limit, along with the recruitment rate demonstrated in the pilot study [10].

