#### 2.2.5 Patients.

Patients who are receiving informal support from the recruited carers will be invited to participate via the provision of data, which will allow their perspectives on HELP implementation to be captured, whilst also facilitating an assessment of the potential, dyadic impact of the intervention. These patients will be eligible to participate if they are: 1) Aged 18 years or older; 2) Physically and mentally able to engage comfortably in conversation and capable of reading written materials; 3) Clinically diagnosed with HF and receiving standard evidence-based HF therapies and either have HF symptoms or one episode of decompensation (symptoms requiring medical attention) in previous six months; 4) Able to speak and understand English; and 5) Receiving regular, unpaid support with managing their condition from a loved one (*i.e.,* a relative or spouse) or friend. Patients will be ineligible if their carers refused to participate in HELP. Carers will remain eligible for participation regardless of patient enrolment. One patient per carer will be invited to participate to enhance sample diversity (approximately 180 patients in total).

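### Table 2's LVEF definition lets one echo fill both time points, which dilutes the change and the effect size passed to the next study

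*Protocol article*

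**What the plan says.** Section 2.3.4 of the protocol article introduces the participant outcomes with the statement (cut one word short here) that "The short and long-term impact of HELP on outcomes for carers and patients will be assessed across data from validated questionnaires, patient diaries, and medical". It adds that "Participant outcome data will be collected at three time points: 1. Baseline, 2. Post-intervention (week six), and 3. Six months post-intervention".

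The last rows of Table 2 cover patient outcomes that are not questionnaire scores. One is "Most Recent LVEF Measurement", sourced from the medical record and marked at baseline and six months post-intervention, but not at week six. The row below is "Hospital Admissions with Reasons over Previous 6 Months", also from the record; this row and the GP-visit row carry a six-month look-back, while the LVEF row has no window. The article describes no echo performed for the study. Section 2.4 has the sites send information from patient records to the central team on data collection forms.

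Section 2.5.1 says of the participant outcomes that "repeated measures analysis of variance will be used to investigate the effect of time point on outcome scores", with "potential effect sizes generated to inform the required sample size for a future definitive evaluation".

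**The concern.** The definition is a positive rule that gives an answer for every patient with any LVEF on file. Applied at six months to someone not re-scanned since baseline, it returns the baseline value. That patient then counts as measured and unchanged, when nothing was measured in the interval.

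The rule also sets no limit on the age of the baseline scan. It would accept as follow-up a scan done after the baseline extraction but before the first HELP session, because section 2.2.9 assigns start dates only after recruitment.

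What is at stake is the LVEF change and its effect size, which section 2.5.1 would carry forward into planning the next study. The more patients are not re-scanned, the more that effect size reflects how often echoes are requested and the less it reflects change in the patients.

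**Working it through.** **Inputs from the article.** Five rollouts × 12 carers × 3 nations = 180 carers, which reproduces the figure in section 2.2.4. With one patient per carer, section 2.2.5 expects about 180 patients. LVEF has two time points, so the repeated measures analysis reduces to a paired t-test (F = t²).

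**Inputs assumed, because the article gives none.** True mean change D = 2 points; SD of change S = 8 points; all n = 180 patients have both entries; whether a patient is re-scanned is unrelated to the change. The share s with no new scan is varied.

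**Formulas.** A share s has a change of exactly 0 and the remaining 1 − s has mean D and SD S. Then:

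- mean recorded change = (1 − s)D
- SD of recorded change = √[(1 − s)(S² + sD²)]
- SE = SD/√180
- standardised effect dz = mean/SD
- paired n for 80% power at two-sided 0.05 = (1.960 + 0.842)²/dz² = 7.849/dz², rounded up
- SE from genuine pairs only = S/√[180(1 − s)]

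**Worked case, s = 50%.** Mean = 0.5 × 2 = 1.0. SD = √[0.5 × (64 + 0.5 × 4)] = √33 = 5.74. SE = 5.74/13.42 = 0.43. dz = 1.0/5.74 = 0.174. Paired n = 7.849 × 33 = 259.01, rounded up to 260. The 90 genuine pairs alone would give mean 2.0 with SE 8/√90 = 0.84.

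| Share re-using one echo | Mean change | SD | SE | Coverage of D by 95% CI | dz | Paired n | Genuine pairs: n, SE |
|---|---|---|---|---|---|---|---|
| 0% | 2.0 | 8.0 | 0.60 | 95% | 0.25 | 126 | 180, 0.60 |
| 25% | 1.5 | 7.0 | 0.52 | 84% | 0.215 | 171 | 135, 0.69 |
| 50% | 1.0 | 5.7 | 0.43 | 36% | 0.174 | 260 | 90, 0.84 |
| 75% | 0.5 | 4.1 | 0.30 | 0.5% | 0.122 | 526 | 45, 1.19 |

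Coverage is from 20,000 simulated studies per row. Intervals from genuine pairs alone covered D about 95% of the time in every row. The paired n only shows the scale of the effect-size distortion; it is not a proposed design.

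**Type I error.** With D = 0, the simulated rejection rate stayed at about 5% for every s. Mean and SE shrink together: at s = 50% the ratio is 1.0/0.43 = 2.3 with copied values and 2.0/0.84 = 2.4 from genuine pairs.

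**Sensitivity to D.** With D = 3 and S = 8, dz without re-use is 3/8 = 0.375. At 25%, 50% and 75% re-use the mean change is 2.25, 1.5 and 0.75, and dz is 0.319, 0.256 and 0.178.

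**The case against.** This is a condensed article. A scan-date field, or a rule for patients without a new scan, could sit in the full protocol or on the data collection forms, neither of which is shown. That limits what can be said about the eventual dataset. It does not repair the printed definition: a date rule elsewhere would have to override the word that tells sites to take the latest value, and the neighbouring rows show that a window was stated where one was intended.

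Section 2.5.1 speaks of outcome scores and never names LVEF, so its inclusion in the repeated measures analysis is a reading of a general sentence. It is the natural reading, since LVEF is listed as a participant outcome with two time points and no other analysis is given.

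LVEF is one of eleven rows in Table 2. Sections 2.5.1 and 3.1 already say that the study lacks power and that participant outcomes will not be definitive. This stands, and it confines the consequence. A disclaimer about power does not, however, cover a value entered twice.

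A reader might go further and infer four things that the article does not support:

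- **That zeros are forced throughout.** They arise only in patients with no new scan, and that share is unknown.
- **That the narrow interval produces false positives.** It does not. The SE is correct for the mean change in the recorded value; the interval is too narrow, and wrongly centred, only as a statement about the patients' actual change. The mean and SD at each single time point are not made tighter.
- **That re-scanned patients are selected by clinical change.** This is plausible but not stated. If it is so, their mean is not the true change of the whole group either.
- **That LVEF says nothing about HELP and must be dropped as an outcome.** This goes beyond the defect.

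**Conclusion.** The point holds as a badly fixed definition. As printed, the rule allows one echo to serve as both baseline and follow-up. The mean change is multiplied by the share re-scanned, and the standardised effect falls by roughly the square root of that share. Under the assumptions above, re-use in half the patients halves the mean change (1.0 instead of 2.0) and cuts the effect size from 0.25 to 0.174. The nominal 95% interval then covers the true change 36% of the time.

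These sizes rest on an assumed change, SD and re-use share, on complete follow-up of 180 patients, and on re-scanning being unrelated to change. The direction of the dilution does not depend on the particular values chosen for the change, SD or share. The consequence is limited to one exploratory outcome in an unpowered, non-randomised study, but that outcome's effect size is among those meant to inform the next study. It should be corrected before data collection.

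**What to change.** In Table 2 and on the data collection form:

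- Record the date of every LVEF value extracted, at both time points.
- Accept a follow-up value only if the scan is dated after the baseline extraction, preferably after the first HELP session.
- Treat a patient without such a scan as having a missing follow-up LVEF, not an unchanged one.
- Report the number of patients with a valid pair, and describe the change in them with the caveat that patients re-scanned in routine care may be a selected group.

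The work is one date field and an edit to Table 2. It is cheap before data collection opens (section 2.8 gives 01/04/2026); recovering dates afterwards would mean returning to the records at five sites. The price is fewer LVEF pairs and a wider interval: under the assumptions used here, SE 0.84 from 90 pairs instead of 0.43 from 180 entries at 50% re-use. No additional scan is implied.
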